## Abstract

**Background:**

Type 2 diabetes (T2D) is associated with limitation in physical performance. Results from animal studies report enhancement of physical performance in T2D rodents treated with sodium glucose cotransporter 2 inhibitors (SGLT2is). However, in human patients with T2D and established atherosclerotic cardiovascular disease (ASCVD) or high cardiovascular risk, the impact of guideline directed SGLT2i medication on physical performance has not been sufficiently examined.

**Objectives:**

The main objectives of this study are thus firstly, to assess the changes in physical performance after 4 weeks of exercise therapy in patients with established ASCVD or high cardiovascular risk categorized into three groups according to their glycemic control at baseline. Secondly, to investigate the association of glycemic control at baseline and new guideline directed antidiabetic treatment (inadequate glycemic control and diabetes + new SGLT2i vs. adequate glycemic control and diabetes vs. no diabetes) with change in physical performance.

**Methods and design:**

This is a 4-week prospective observational study of 450 participants with established ASCVD or high cardiovascular risk with or without T2D and without previous SGLT2i medication undergoing exercise therapy during inpatient rehabilitation in a single center in Switzerland. Upon admission, participants are categorized into 3 groups of 150 participants each according to their glycemic control. Group I consisting of participants with inadequately controlled T2D defined as mean fasting plasma glucose (FPG) of ≥7 mmol/L, who are consequently administered new treatment with an SGLT2i. Group II comprises of participants with adequately controlled T2D with mean FPG of <7 mmol/L requiring no antidiabetic medication change. Group III consists of participants with no diabetes and mean FPG of ≤ 5.5 mmol/L. Primary outcomes are 6-min walk distance and rate of perceived exertion. Secondary outcomes are echocardiographic parameters (left ventricular mass index; global longitudinal strain average; end-diastolic volume), fatigue, muscle, metabolic, and anthropometric measures.

**Ethics and dissemination:**

This study is conducted in accordance with the Declaration of Helsinki with ethical approval from the Cantonal Ethical Commission of Bern, Switzerland. The results will be published in a peer-reviewed journal. The implementation and reporting will be according to the SPIRIT guidelines.

**Study protocol registration:**

https://www.clinicaltrials.gov/, identifier: NCT03422263.

## Introduction

Type 2 diabetes (T2D) has been associated with limitation in physical performance in individuals with or without atherosclerotic cardiovascular diseases (ASCVD) (1–4). These impairments in physical performance, measured as submaximal or maximal exercise capacity, manifest even with adequate glycemic control and in the absence of overt signs or symptoms of established ASCVD (1, 4–6). This is of clinical relevance because low physical performance in addition to poor glycemic control strongly predicts long-term cardiovascular mortality in individuals with T2D (7–11).

Accordingly, improvement of exercise capacity is considered an important prevention and therapeutic target in existing guidelines to alleviate the risk of atherosclerotic cardiovascular events and mortality in individuals with T2D and/or ASCVD (12–15). Furthermore, because independent of diabetes, fasting plasma glucose is associated with risk of ASCVD, the guidelines also highlight the need for adequate glycemic control (11, 15). Consequently, algorithms for the use of medical therapy have been developed in recent years for the treatment of T2D based on individualized cardiovascular risk profiles with sodium glucose cotransporter 2 inhibitors (SGLT2is) being recommended mainly for individuals with congestive heart failure, established ASCVD or high cardiovascular risk (16–19). These recommendations are based on the results of major cardiovascular outcome trials on SGLT2is, namely empagliflozin, dapagliflozin, and canagliflozin, in patients with T2D which showed that this drug class consistently reduces the risks of heart failure hospitalisations, progression of renal disease as well as moderately reduces the risk of major adverse cardiovascular events, or at least some features of them (20–23). Data suggest these benefits are independent of glycemic control and can be apparent early upon initiation of treatment (24). However, the precise mechanisms of these benefits remain unclear.

Based on recent studies in animals, a possible mechanism can be the enhancement of exercise capacity after 4 weeks of SGLT2i treatment in murine models of T2D and heart failure. The results showed that lowered exercise capacity was restored through central and peripheral mechanisms by improvement of myocardial function and activation of skeletal muscle fatty acid oxidation (25, 26). In humans, although a few studies with small sample sizes suggested that empagliflozin was associated with early improvement in exercise capacity in T2D patients with heart failure (27, 28), others could not replicate these findings on empagliflozin and canagliflozin (29, 30). In a randomized, double blinded study of exercise therapy and dapagliflozin vs. exercise therapy and placebo, dapagliflozin treatment resulted in higher increase in peak exercise capacity from baseline when compared with exercise therapy and placebo despite elevated fasting plasma glucose levels and abrogated increased insulin sensitivity when compared to exercise therapy and placebo (31). These findings suggest that the influence of dapagliflozin on physical performance measured as peak exercise capacity may possibly be independent of glycemic control and that when combined with exercise therapy as recommended by guidelines, dapagliflozin may even contribute to a poorer glycemic control.

To the best of our knowledge, the above findings have not been examined patients with T2D and established ASCVD or high cardiovascular risk, as such, in patients where guideline recommendations strongly favor both improvement of physical performance and first-line medical therapy with an SGLT2i (15, 19).

Given this background, the main aims of this study are firstly, to investigate the changes in physical performance and glycemic control 4 weeks after initiation of guideline-directed medical therapy of an SGLT2i and exercise therapy in patients with established ASCVD or high cardiovascular risk and T2D with initial inadequate glycemic control; secondly, to investigate the changes in physical performance and glycemic control 4 weeks after exercise therapy only in patients with established ASCVD or high cardiovascular risk and T2D with adequate glycemic control; thirdly, to investigate the changes in physical performance 4 weeks after exercise therapy only in non-diabetic patients with established ASCVD or high cardiovascular risk; and fourthly to investigate the cross-sectional and longitudinal association of glycemic control at baseline and new guideline directed antidiabetic treatment (inadequate glycemic control and diabetes + new SGLT2i vs adequate glycemic control and diabetes vs. no diabetes) with physical performance and other outcomes influencing physical performance (secondary outcomes), in patients with established ASCVD or high cardiovascular risk after adjusting for baseline covariates.

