## Methods and analysis

### Study design

The PUSH is a real-world, 4 week prospective, three-arm observational study of patients with established ASCVD or high cardiovascular risk with and without T2D undergoing regular exercise therapy during inpatient rehabilitation in a single center in Switzerland. Employing a multi-group design and a two-step analytic approach, the study investigates the changes in physical performance (and glycemic control) in 3 categories of glycemic control after 4 weeks. Furthermore, the associations between the 3 categories of glycemic control and new guideline directed antidiabetic treatment (inadequate glycemic control and diabetes + new SGLT2i vs. adequate glycemic control and diabetes vs. no diabetes) with physical performance are evaluated in cross-sectional and prospective analyses. A flow chart of the study is shown in Figure 1.

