### Study group categories

Glycemic control was assessed within the first 3 days upon admission by measurement of fasting plasma glucose (FPG) with the widely used diagnostic cut-off of ≥7 mmol/L employed to define inadequate glycemic control (33, 36). Hemoglobin A_1c_ (HBA_1c_) testing was equally done in all participants upon admission but was not used to define inadequate glycemic control in this cohort to circumvent the bias linked to participants with conditions that affect erythrocyte turnover such as acute bleeding and/or erythrocyte transfusion during the acute hospitalization prior to rehabilitation (33). HbA_1c_ was however used as one of the parameters to distinguish participants with diabetes or impaired glucose metabolism from those with normal glucose metabolism as described below.

Depending on their glycemic control upon admission and following guideline recommendations, participants were categorized to one of three groups using clinically defined cut-off categories of FPG levels as follows (11):

Group I: Participants with inadequately controlled T2D defined as mean FPG of ≥7 mmol/l within the first 3 days upon admission under other standard of care medication, who were afterwards administered *de novo* SGLT2i treatment; namely either canagliflozin 100 mg, or dapagliflozin 10 mg, or empagliflozin 10 mg once daily, with the choice of which of the SGLT2is being at the discretion of the individual treating physician,

Group II: Participants with adequately controlled T2D, previous diagnosis of T2D or use of antidiabetic medication, with mean FPG <7 mmol/L; and participants with impaired fasting glycemia (IFG) or pre-diabetes, defined as mean FPG of 5.6–6.9 mmol/L and HbA_1c_ levels of 5.7–6.4 % (15, 33), under other standard of care treatment and no SGLT2i,

Group III: Participants with no previous diagnosis of T2D or use of antidiabetic medication and normal glucose metabolism defined as FPG of ≤ 5.5 mmol/L under other standard of care treatment and no SGLT2i were included as a reference group as previously described in the meta-analysis of prospective studies on diabetes mellitus, FPG, and risk of vascular disease (11).

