### Outcome measures: Assessment, blinding, and rationale

The PUSH assessed objective and subjective outcomes of physical performance in addition to hemodynamic, cardiorespiratory, and cardiometabolic risk variables. Outcome assessments were done upon admission (baseline), facultatively at week 2 and at week 4 (Table 1). All participants, direct care providers and assessors were masked to the outcomes under investigation throughout the study. Whereas, participant and care providers were blinded by categorically withholding supplementary information on the glycemic control categories described above and exposures under investigation, main outcome assessors (therapists and laboratory technicians) were masked by complete prohibition of access to patient medication data as per previously established institutional policy.

**Table 1 T1:** Assessment time plan.

**Assessment**	**Time points during study**		
	**Baseline** ^a^	**Week 2**	**Week 4**
Screening for inclusion and exclusion criteria	°		
Participant characteristics^b^	°		
Status of medications^c^	°	°	°
Anthropometric and clinical parameters^d^	°	°	°
Laboratory tests^e^	°	°	°
Rehabilitation outcomes^f^	°	°	°
Transthoracic echocardiography^g^	°		°
Sonographic assessment of liver parenchyma (NAFLD)^h^	°		°
Muscle sonography^i^	°	°	°
Monitoring for adverse events^j^	Throughout stay		

a *Baseline was defined as the date of eligibility confirmation and inclusion in the study. If no data were available at baseline, the most recent data from the hospitalization prior to admission were used*.

b
*Included information on age, sex, medical history, complications and comorbidities, smoker status, coffee consumption.*

c
*Included antidiabetic agents, antihypertensives, lipid-lowering drugs, thrombocyte aggregation inhibitors, therapeutic anticoagulation, use of proton pump inhibitors, uric acid lowering drugs, antidepressants, opiates, NSAIDs, neuropathic pain treatment, vitamin D, iron, calcium, and magnesium substitution.*

d
*Included body weight, BMI, waist and hip circumferences, estimation of skeletal muscle mass in kg using the Baumgartner equation, mean systolic and diastolic blood pressures, mean fasting plasma glucose (for all groups at baseline, for group I and II at week 2 and 4), peak expiratory flow rate, state of nocturia, pain numeric rating scale [NRS] (range 1–10).*

e

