#### Data analyses

Demographic data will be examined using independent-samples *t*-tests and Fisher's exact tests for dichotomous variables. Independent-samples *t*-tests and repeated-measures ANOVAs will be employed to compare changes in physical performance after 4 weeks. Differences between primary and secondary outcome variables after 4 weeks will also analyzed by linear mixed-effects models (LMMs). The time factor for the model will be set at baseline and week 4. The models will include model-based adjustments for baseline characteristics influencing physical performance in such cohorts: (1) age, sex, BMI, waist circumference, diabetes duration and history of cardiovascular disease.

To minimize the bias that could result from participants in the 3 groups having highly variable duration of stay, the prospective analyses will be performed on a modified intention-to-treat and per protocol basis. The modified intention-to-treat population will be defined as participants who have been categorized to a study group and have at least one follow-up measurement of the primary outcomes, regardless of treatment adherence or duration of stay. The “last observation carry-forward method” will be used in the absence of complete follow-up data. For “per protocol” analysis, only those participants who have follow-up measurements after a minimum treatment duration or length of stay of ≥20 days will be included.

Sensitivity analyses will be performed to account for potentially non-ignorable missing data due to dropout as well as the possible impact of other potentially influential variables. A Bonferroni correction will be applied to the LMM analyses of the primary and secondary outcomes.

Pre-specified subgroup analyses will be conducted; these will include subgroups defined according to the various entities of ASCVD, gender, age groups, and other factors.

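### Four-week change in fasting glucose is read within groups cut at 7 mmol/L on that same baseline glucose, so part of the fall in Group I, and of any rise in the T2D part of Group II, is regression to the mean

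*Protocol article*

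**What the plan says.** All references are to the protocol article.

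- **Aims (Introduction).** The first aim is "to investigate the changes in physical performance and glycemic control 4 weeks after initiation of guideline-directed medical therapy of an SGLT2i" together with exercise, in T2D with inadequate control. The second asks for the same changes after exercise only, in T2D with adequate control. The third, in people without diabetes, does not include glycemic control.
- **Study design.** The change is read by group: "the study investigates the changes in physical performance (and glycemic control) in 3 categories of glycemic control after 4 weeks".
- **Study group categories.** Group I is "Participants with inadequately controlled T2D defined as mean FPG of ≥7 mmol/l within the first 3 days upon admission", and these participants then start an SGLT2i. Group II has two parts. One is T2D under adequate control, that is, known or treated diabetes whose mean FPG lies below the 7 mmol/L cut. The other, for which an HbA1c criterion also applies, is "participants with impaired fasting glycemia (IFG) or pre-diabetes, defined as mean FPG of 5.6–6.9 mmol/L".
- **Table 1 and its notes.** The schedule has "mean fasting plasma glucose (for all groups at baseline, for group I and II at week 2 and 4". HbA1c is routine at admission only. No second baseline, separate from the one used for grouping, is described.
- **Data analyses.** For physical performance, "repeated-measures ANOVAs will be employed to compare changes in physical performance after 4 weeks". Mixed models with baseline and week 4 as time points cover the primary and secondary outcomes. The listed adjustment variables are age, sex, BMI, waist circumference, diabetes duration and cardiovascular history; baseline FPG is not among them.
- **Discussion.** The limitations concede that the design is not randomised and that selecting on glycemic control is a threat. Regression to the mean is not mentioned.

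**The concern.** FPG does two jobs here: it decides the group, and it is the starting point of the change. A person whose true level is near 7 mmol/L lands in Group I more readily if the first readings happened to be high, and in the T2D part of Group II if they happened to be low. At week 4 those chance deviations are not repeated, so the two groups drift toward each other with no treatment effect at all.

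Everyone in Group I starts an SGLT2i, so no untreated group with FPG of 7 or more can show how large the drift is. A paired change in Group I therefore mixes SGLT2i, exercise and artefact. The sign matters: the Introduction cites a trial suggesting that dapagliflozin combined with exercise may worsen glycemic control. A built-in fall in Group I could hide such a signal or look like a benefit.

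**Working it through.** **Plan's own figure.** There is none to reproduce. The article gives no FPG mean, variance, repeatability or expected change, so every FPG input below is an assumption. Only the 7 mmol/L cut, the 5.6–6.9 mmol/L window and the 130 evaluable participants per group come from the article.

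**Formula, no true change.** Let observed baseline FPG in T2D be normal with mean μ and SD σ, let ρ be the baseline-to-week-4 correlation, and z = (7 − μ)/σ. Then

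- Group I shift = −(1 − ρ) σ φ(z) / (1 − Φ(z))
- T2D part of Group II shift = +(1 − ρ) σ φ(z) / Φ(z)

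**Range by correlation.**

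- *Illustration:* μ = 7.2, σ = 1.8, ρ = 0.7. z = −0.111, φ = 0.3965, 1 − Φ = 0.5442, Φ = 0.4558, (1 − ρ)σ = 0.54. Shifts: −0.54 × 0.3965/0.5442 = −0.39 and +0.54 × 0.3965/0.4558 = +0.47. Gap 0.86 mmol/L.
- *Upper end:* μ = 7.5, σ = 2.0, ρ = 0.6. z = −0.25, φ = 0.3867, (1 − ρ)σ = 0.80. Shifts −0.52 and +0.77. Gap 1.29.
- *High correlation:* μ = 7.0, σ = 1.5, ρ = 0.85. (1 − ρ)σ = 0.225, φ = 0.3989, each shift 0.225 × 0.3989/0.5 = 0.18. Gap 0.36.

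**Allowing for averaging.** Grouping uses a mean over the first 3 days; the number of readings is not stated. With between-person SD s_b, within-person SD s_w and k independent readings, σ² = s_b² + s_w²/k and ρ = s_b²/σ². Take μ = 7.5, s_b = 2.0, s_w = 1.0:

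| Readings | σ | ρ | Group I | T2D part of Group II | Gap |
|---|---|---|---|---|---|
| 1 | 2.24 | 0.80 | −0.30 | +0.42 | 0.72 |
| 3 | 2.08 | 0.92 | −0.10 | +0.15 | about 0.25 |

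With s_b = 1.5 instead, the three-reading gap is 0.33 to 0.35; with s_w = 0.5 and three readings it is below 0.1. At 130 per group, the Group I shift in the table is about 2.5 standard errors with one reading and 1.5 with three.

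Simulation over 48 scenarios (μ 6.5–8.0, s_b 1.5–2.0, s_w 0.5–1.5, one or three readings) gave a Group I fall in all 48 (0.02 to 1.00 mmol/L) and a rise in the T2D part of Group II in all 48 (0.03 to 1.19). The largest values come from a single reading with s_w as large as s_b (ρ = 0.5), an extreme case.

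**Group II as a whole.** The prediabetes part is also cut from below, at 5.6 mmol/L. Simulated for a non-diabetic population with mean 5.2–6.1 mmol/L, its shift is −0.60 to +0.05, and downward whenever that mean is 5.2–5.8. If the T2D part rises by u and the prediabetes part moves by p < 0, the net is zero at a prediabetes share of u/(u − p). Examples: 0.43/(0.43 + 0.17) = 0.72; 0.15/(0.15 + 0.35) = 0.30. Over the 20 pairs tried, the break-even share runs from about 11% to 72%. The article does not give the share.

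**Does conditioning on baseline remove it?** Under joint normality, expected week-4 FPG is linear in observed baseline FPG, and group is a function of that same value, so with no effect the group coefficient is zero. Simulation in the scenario tabulated above agrees: the coefficient is within 0.003 of zero for one and for three readings, while the raw changes are those in the table.

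**The case against.** **The size may be small.** This stands. Averaging over 3 days shrinks the artefact to roughly a third if the readings are three and independent, and neither condition is stated. A reader might take 0.86 mmol/L as the size; it is one illustration, and well under 0.3 is also plausible. In the other direction, true drift over 4 weeks, or a baseline filled in from the preceding hospital stay as Table 1 permits when data are missing, would lower the correlation and enlarge it.

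**Group II need not rise.** This stands for Group II as defined in Study group categories. A reader might infer a false rise in the whole group, but the prediabetes part tends to move the other way. The rise holds for adequately controlled T2D, which is the population of the second aim.

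**Post-acute recovery is a different thing.** Fading stress hyperglycaemia would lower glucose in both groups. It would add to the Group I fall and offset a Group II rise, so it cannot be counted as moving both groups toward the mean.

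**No FPG test is named, and causal claims are disowned.** Partly stands. The repeated-measures ANOVA sentence concerns physical performance, FPG is not itemised among the secondary outcomes, and the Discussion disclaims causal conclusions. It would be unfair to say that the authors will credit the drug with the whole fall. But glycemic change is written into the first two aims, and a general warning about selection does not tell a reader that the paired change is biased in a known direction.

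**The primary outcomes.** A reader might extend the point to 6-minute walk distance or Borg exertion. Neither was used to form the groups, so this artefact does not reach them.

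**Conclusion.** The point holds for the glycemic part of the first two aims. The same baseline FPG both forms the groups and starts the change, no other glycemic measure is routinely repeated, and nothing in the stated analysis conditions on it. Some artefactual fall in Group I and some artefactual rise in the T2D part of Group II follow whenever FPG fluctuates within persons. The direction in those two sets is firm; the net direction in Group II is undetermined.

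The size cannot be fixed from the article. Under roughly normal FPG and the assumed values above, the false gap between the two T2D sets runs from about 0.25 mmol/L or less (three-reading baseline, within-person SD 1.0 or lower, between-person SD 2.0) to about 1.3 mmol/L (correlation 0.6, SD 2.0). At the low end the Group I artefact alone would not normally reach significance at 130 participants; at the high end it would.

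**What to change.** 1. Report raw within-group FPG change as descriptive only, and name regression to the mean among the limitations, separately from the general remark on selection.
2. In participants with T2D (Group I and the T2D part of Group II), add a model of week-4 FPG on the group (SGLT2i) indicator plus continuous baseline FPG. The baseline value must be the same first-3-day mean that decided the group.
3. Interpret the group coefficient as an estimate near 7 mmol/L. Check the linear form, since curvature can pass for a jump. Check also for selection at the cut-off: patients who declined guideline-directed therapy were excluded, which may act on one side only, and filling groups to 150 can distort the numbers on either side.
4. Report the prediabetes share of Group II and show FPG change separately for its two parts.

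A regression-discontinuity analysis of walk distance is optional; this artefact does not call for it.

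**Cost.** One additional model on data already collected (Study status reports collection complete). The interval widens because group and baseline FPG are strongly related. For a normal baseline cut at z = −0.24 (the three-reading case above), their squared correlation is φ²/[Φ(1 − Φ)] = 0.3876²/(0.4051 × 0.5949) = 0.62. The standard error is then √(1/(1 − 0.62)), about 1.6 times what it would be if the two were unrelated. The estimate is local and does not describe patients far above 7 mmol/L.

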### Rehabilitation program

The research was conducted in a single center at an altitude of 1,600 m in the Bernese Swiss Alps in Crans-Montana, Switzerland. All participants were exposed to supervised exercise therapy as follows: eight to twelve 30-min-sessions per week of physical activity, of which 4–5 sessions were aerobic exercises in a pool, on a cycloergometer, treadmill or outdoor moderate intensity walking, 2–3 sessions of muscle strengthening through resistance and stretching exercises, 2–4 sessions of occupational activity, proprioceptive and range of motion exercises supervised by blinded certified therapists. Exercise intensity was determined according to the rate of perceived exertion measured using the Borg category ratio (CR-10) as previously described (37, 38). Intensity was increased progressively according to the patient's tolerance. In addition, 30-min sessions of auxiliary non-physical activity with a dietician, psychologist, acupuncturist, art therapist or social worker were planned as needed.

For the PUSH study, participant motivation and participation were measured based on the session reports of blinded therapist during weekly interdisciplinary meetings using the Pittsburgh rehabilitation participation scale as previously described (39).

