### Sample size and data analysis

#### Sample size

Based on the results of the cardiovascular heart study of Enright et al., among 2,281 community dwelling adults ≥68 years old, the expected mean 6-min walk distance (6MWD) was 344 ± 88 m which is the set target of exercise therapy in rehabilitation (45). Centered on our clinical observations and on the results of a small pilot study in the clinical rehabilitation of patients with cerebrovascular disease (121), we assumed a mean 6-MWD at baseline of 250 m with an anticipated improvement of 80 ± 40 m after 4 weeks of exercise therapy. To detect an additional difference of ±15%, as reported in previous studies on this subject (28), within the group as well as between any 2 groups with power of 80 % and an alpha error of 5% using a 2-sided test after 4 weeks, the sample size required was 130 participants per group. Based on our admission statistics, the attrition rate for administrative reasons, mainly being lack of insurance coverage for a treatment duration of at least 20 days, was estimated at 15 %, while 85 % of participants were expected to complete the week 4 follow-up. To this end, 150 participants per group needed to be enrolled (450 participants in total).

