The PUSH design however has some limitations. First, the non-randomized design precludes analyses and conclusions of the causal relationships among variables. Second, despite efforts to address the internal validity threats, the selection bias of using glycemic control to determine participants for the guideline-directed medical therapy with an SGLT2i remains an important threat in the interpretation of the results even though a previous study in this field did not show any negative impact of suboptimal glycemic control under treatment with an SGLT2i (dapagliflozin 10 mg) on the physiological adaptation to endurance exercise training (31). Accordingly, studies on changes in physical performance under SGLT2is in patients with both inadequately and adequately controlled T2D are still warranted. Third, the prospective design of this study with a follow-up of just 4 weeks addresses solely the hypothesis of early changes in physical performance under guideline-directed medical therapy with an SGLT2i. Further studies will be necessary to investigate, if present, the extent and sustainability of these early changes over a longer period of observation with or without endurance exercise therapy. Finally, we will not compare participants to those who did not receive inpatient rehabilitation after a medical or surgical condition warranting inpatient rehabilitation, as such, the potentiating effect of exercise therapy during rehabilitation on the results shall not be easily quantified.

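### The Sample size section claims 80% power for an additional 15% both within a group and between two groups, but a within-group change cannot isolate an additional difference and one n cannot give 80% for both

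*Protocol article*

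**What the plan says.** The Introduction lists four aims. The first, in Group I, is "to investigate the changes in physical performance and glycemic control 4 weeks after initiation of guideline-directed medical therapy of an SGLT2i and exercise therapy". The next two are the matching changes in the other groups: "secondly, to investigate the changes in physical performance and glycemic control 4 weeks after exercise therapy only" in adequately controlled diabetes, and "thirdly, to investigate the changes in physical performance 4 weeks after exercise therapy only in non-diabetic patients". The last is "fourthly to investigate the cross-sectional and longitudinal association of glycemic control at baseline and new guideline directed antidiabetic treatment", adjusted for baseline covariates.

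Under Rehabilitation program: "All participants were exposed to supervised exercise therapy as follows". Exercise is therefore common to all three groups, and the new SGLT2i is given only in Group I.

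The Sample size section assumes a baseline 6-minute walk distance of 250 m "with an anticipated improvement of 80 ± 40 m after 4 weeks of exercise therapy". It then asks for an additional difference of ±15%, "within the group as well as between any 2 groups with power of 80" percent, two-sided alpha 5%, and arrives at 130 per group (150 enrolled).

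Data analyses compares changes by independent-samples t-tests and repeated-measures ANOVA, then by adjusted linear mixed models.

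**The concern.** The power statement attaches one target, one n and one power to two different quantities.

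- **Between groups.** The difference in 4-week change between Group I and another group can hold something additional to exercise, because both sides of the contrast had exercise. It still carries the confounding that the Discussion admits.
- **Within a group.** The change from baseline in Group I is the exercise gain plus any drug effect. Nothing inside Group I separates the two. The only within-group comparison that gives the word additional a meaning sets the observed change against a fixed 80 m. The plan takes that figure from clinical observation and a small pilot in cerebrovascular rehabilitation, and treating it as known leaves its uncertainty out of the test.

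At stake is a stated power property that the design does not have as written. A reader of the results could take the within-group clause as support for judging the SGLT2i from the Group I change alone.

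**Working it through.** **Inputs** (Sample size section): expected gain 80 m; SD 40 m, taken here as the SD of the 4-week change; two-sided alpha 5%; power 80%; n = 130 per group. Assumption: 15% is 15% of the expected gain, 0.15 × 80 = 12 m. The text does not say what the 15% is a percentage of.

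**1. The plan's own figure.**
- Between two groups: n = 2 × (1.960 + 0.842)² × 40² / 12² = 174.4, so 175 per group.
- Within a group against a fixed value: n = (1.960 + 0.842)² × 40² / 12² = 87.2, so 88.
- Neither is 130. The nearest match found is 15% of the gap between the 344 m target and the 250 m baseline: 0.15 × 94 = 14.1 m, which gives 127 per group for the two-group comparison. The document does not state that basis.

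**2. Power at n = 130 for 12 m, SD 40 m** (noncentral t)

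| Comparison | Standard error | Noncentrality | Power |
|---|---|---|---|
| Within a group, against a fixed 80 m | 40/√130 = 3.51 m | 12/3.51 = 3.42 | about 92% |
| Between two groups, difference in change | 40 × √(2/130) = 4.96 m | 12/4.96 = 2.42 | about 67% |

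**3. Does the mismatch depend on reading 15% as 12 m?** The exact percentages do. The mismatch does not, because the between-group standard error is √2 times the within-group one. With SD 40 m, the difference detectable with 80% power at n = 130 is
- within a group: 2.802 × 3.51 = 9.8 m;
- between two groups: 2.802 × 4.96 = 13.9 m.

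No single difference gives 80% for both. At 14.1 m the between-group power is about 81% and the within-group power about 98%.

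**4. How far the within-group reading leans on the 80 m.** If the true exercise gain is exactly 80 m and the drug does nothing, the test against 80 m rejects about 5% of the time. If the true gain differs from 80 m by 5, 10 or 15 m, still with no drug effect, the one-sample test at n = 130 and SD 40 m rejects about 29%, 81% or 99% of the time. These errors are illustrations; the document gives no estimate of how uncertain the 80 m is.

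**The case against.** A reader might infer something stronger: that the first aim tests the drug by a pre-post comparison that succeeds whatever the drug does. The arithmetic is easy. With a gain of 80 m from exercise alone, 80/(40/√130) = 22.8, so a test against zero change would reject practically always with no drug effect.

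The document does not support that reading.
- The first aim names both exposures, and the second and third aims supply the exercise-only changes beside it.
- The treatment question sits in the fourth aim as a covariate-adjusted comparison, and Study design describes a two-step approach.
- Data analyses names no paired or one-sample test in Group I and ties no decision to one.
- The Discussion remark that the study "addresses solely the hypothesis of early changes in physical performance under guideline-directed medical therapy with an SGLT2i" is a limitation about the 4-week follow-up. It does not define a within-group hypothesis.
- The Discussion also says that the non-randomized design precludes causal conclusions and admits selection by glycemic control.

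All of this stands, and the near-certain rejection describes a test that the plan does not name. Whether the changes in aims one to three are reported with or without a p-value is a matter of reporting style.

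Two further defenses carry part of the way. First, a test against the expected 80 m is a coherent reading, and it holds its 5% level if 80 m is right. Second, one n may be meant as enough for the harder comparison, with power to spare on the easier. That works if the target is 14.1 m (81% and 98%). It fails at 12 m, where the between-group comparison has about 67%. Neither defense gives a within-group contrast an additional component without an external benchmark.

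**Conclusion.** The concern holds for the power statement. As written, the Sample size section claims 80% power for an additional difference within a group. The design cannot isolate such a difference there except against an assumed 80 m. The same 80% is claimed for the between-group comparison, whose standard error is √2 times as large. On 12 m and SD 40 m, the powers at 130 per group are about 92% and 67%. On the unstated 14.1 m basis the between-group figure would be about 81%. All these figures rest on 40 m being the SD of change.

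The verdict does not extend to a claim that the study judges the SGLT2i from the Group I change. The aims, the analysis section and the stated limitations point to the adjusted between-group association. What the text lacks is a sentence saying so.

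The between-group contrast does not isolate the drug either: new SGLT2i use coincides with fasting plasma glucose of 7 mmol/L or more, so it is confounded by glycemic control.

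**What to change.** 1. **Sample size.** Delete the within-group clause. State the power, or the detectable difference, for the between-group difference in 4-week change only. Say what the 15% is a percentage of and that 40 m is the SD of change, if it is. On the 12 m reading this means reporting about 67% power, or a detectable difference of 13.9 m at 80%.
2. **Introduction (aims) and Data analyses.** State that the Group I change in the first aim reflects exercise and SGLT2i together. State that any statement about the new SGLT2i rests on the adjusted between-group difference in change. Keep the caveat that this contrast is confounded by glycemic control and is not causal.

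The cost is wording, plus a less favorable stated power if 12 m is the intended target. Data collection is complete at 450 participants, and the change needs no new patients, data or clinical procedures.
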